#### Sociodemographic and clinical data

Sociodemographic data such as age, level of education, marital status, living situation, medication use (including alternative medications or therapies) and lifestyle variables (e.g. smoking) are obtained by questionnaire.

Clinical information, including date of diagnosis, stage and subtype of disease, and treatment history is obtained from medical records. During the follow-up period, data on disease status (response to treatment, progression or relapse) and data on any additional treatment are collected.

#### Moderating variables

At baseline, a series of questions is used to assess a number of potential moderating variables, including pre-illness lifestyle (frequency, nature and intensity of daily physical activity and exercise behaviour, or avoidance thereof), current attitudes towards and beliefs about exercise and daily physical activity in general, and about exercising after chemotherapy. These questions are adapted from measures developed by Courneya and colleagues [41,42] for use in evaluating exercise in cancer survivors, and are based on established health behaviour theories, in particular the Theory of Planned Behaviour [42].

#### Costs from a societal perspective

Besides the costs of the exercise programmes, data on health care costs, patient and family costs, and costs of production losses are collected using cost diaries administered on a 3-monthly basis during the entire follow-up period. Health care costs include the costs of oncological care, general practice care and physiotherapy, additional visits to other health care providers, prescription of medication, professional home care and hospitalization. Patient and family costs include out-of-the-pocket expenses such as travel expenses, over-the-counter medication, and costs for paid and unpaid help. Costs related to production losses include work absenteeism for patients with paid jobs, and days of inactivity for patients without a paid job.

### Power calculations

Power calculation is based on the effects on physical fitness and fatigue found in the study by De Backer et al. [13] examining the long-term effects of a high intensity resistance and endurance exercise programme after cancer treatment compared with natural recovery.

With a sample size of 80 we are able to detect a difference in fatigue of 9 points (EORTC QLQ-C30), with a standard deviation (SD) of 20, a power of 0.80 and two sided alpha of 0.05. Additional power calculations (a power of 0.80 and alpha of 0.05) for muscle strength (vertical row) and cardiorespiratory fitness (peakVO_2_) showed that this sample size enables us to detect a difference in vertical row of 0.09 1-RM/kg (SD 0.20) and a difference in peakVO_2 _of 3 ml/min/kg (SD 7). Both supplementary calculations are based on differences in results reported by the same research group [13].

To compensate for dropouts and taking into account the multi-level design we aim to enrol 40% more patients, therefore in total 120 subjects per group. Since we expect smaller differences between the high intensity exercise group and the low-to-moderate intensity exercise group, we have decided to enlarge these two groups to 140 subjects per group. The waiting list control group will consist of 120 patients.

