### Primary outcome measures

#### Cardiorespiratory fitness

Cardiorespiratory fitness is measured during a maximal exercise test on an electronically braked cycle ergometer according to a ramp protocol [29], in which the resistance gradually increases every six seconds aiming to achieve the maximum within 8 to 12 minutes. All patients are instructed to cycle with a pedal frequency between 70 and 80 RPM, and are encouraged to continue exercising until exhaustion, or inability to maintain the pedal frequency of 70 RPM. Expired gases are collected and analyzed breath by breath for O_2_, CO_2_, and volume. The average values of the last 30 seconds of exercise are used as measures for peak oxygen uptake (peakVO_2_, in l/min), peak power output (peakW, in watt), and peak HR. Ventilatory threshold is determined by the oxygen equivalent method [30], using the average value obtained by two independent observers. HR and respiratory exchange ratio (RER) are used as objective criteria for peak exercise.

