**A. Primary outcome measures**	

Cardiorespiratory fitness	Maximum exercise test (peakVO_2 _)

Muscular strength	30 s sit-to-stand test, maximal handgrip strength

Fatigue	Multidimensional Fatigue Inventory (MFI) [38] and the Fatigue Quality List (FQL) [40] questionnaires

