**B. Secondary outcome measures**	

Sociodemographic data	Age, education, marital status, living situation, comorbidities and life style variables (e.g. smoking)

Clinical data	

Medical history	Date of diagnosis, subtype of disease, stage of disease, history of therapy

Disease status and treatment	Response to treatment, progression or relapse of disease and data on any additional treatment will be recorded from medical records

Adverse events	Medical records, reports of the sports physician and physical therapist

Physical tests	

Physical examination	Height, weight, waist and hip circumferences, four skinfolds (biceps, triceps, suprailiacal and subscapular)

Body composition and bone mineral density	Dual Energy X-ray (DXA) scan

Questionnaires	

Health-related quality of life	EORTC Quality of Life Questionnaire C30 (EORTC QLQ-C30) [43], EuroQol (EQ5D) [44], EORTC Chemotherapy-induced peripheral neuropathy module (QLQ-CIPN20) [45]

Physical activity	Physical Activity Scale for the Elderly (PASE) [46], Recordings of the Actitrainer accelerometer (Actigraph, Fort Walton Beach Florida, USA)

Mood disturbance	Hospital Anxiety and Depression Scale (HADS) [47,48]

Functioning in daily life	Impact on Participation and Autonomy (IPA) [49]

Quality of Sleep	Pittsburgh Sleep Quality Index (PSQI) [50]

Return to work	Return to work questionnaire

Moderating variables	Questionnaire about pre-illness lifestyle, current attitudes toward and beliefs about exercise in general

Satisfaction with the intervention	Satisfaction questionnaire

Cost questionnaires	Cost dairies

Compliance with the exercise program	Self-report and objective measures (e.g. attendance, exercise logs, target intensity)

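### The stated 0.80 power is for non-primary measures of fatigue and muscle strength, and for peakVO2 on a different scale from its definition

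*Protocol article*

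**What the plan says.** All references are to the protocol article.

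**Fatigue.** Table 1, part A, gives the primary instruments as "Multidimensional Fatigue Inventory (MFI) [38] and the Fatigue Quality List (FQL) [40] questionnaires", and the Fatigue section under Primary outcome measures agrees. The Power calculations section uses another instrument: "With a sample size of 80 we are able to detect a difference in fatigue of 9 points (EORTC QLQ-C30"). The remaining inputs to that calculation follow in the same sentence: "with a standard deviation (SD) of 20, a power of 0.80 and two sided alpha of 0.05". Table 1, part B, places that instrument among the secondary outcomes, under health-related quality of life: "EORTC Quality of Life Questionnaire C30 (EORTC QLQ-C30) [43"].

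**Muscle strength.** Table 1, part A, gives "30 s sit-to-stand test, maximal handgrip strength", and the Muscle strength section describes the same two tests. The power calculation is for "a difference in vertical row of 0.09 1-RM/kg (SD 0.20"). Apart from that calculation, vertical row appears only as the first of the six resistance exercises in the training programme. It is in neither part of Table 1.

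**Cardiorespiratory fitness.** Table 1, part A, lists peakVO2 from the maximal exercise test, without a unit. The Cardiorespiratory fitness section defines it as "peak oxygen uptake (peakVO_2_, in l/min"). The power calculation uses a difference "of 3 ml/min/kg (SD 7").

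**The concern.** A power statement tells the reader how large an effect on the primary outcome the trial can reliably find. It does so only if the difference and the SD belong to that outcome. Here the fatigue and strength inputs belong to other measures. A 9-point difference with an SD of 20 on the QLQ-C30 says nothing direct about an MFI subscale or an FQL score. A difference in vertical-row load per kg says nothing direct about kilograms of grip force or the number of chair stands. For peakVO2 the quantity is the right one, but its difference and SD are on a body-weight scale that the outcome definition does not use.

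Interpretation is at stake. If the trial finds no difference on the MFI or on handgrip, a reader who turns to the stated 0.80 power will take the result as more informative, or less, than it is. The document offers no figure to check this against.

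**Working it through.** **1. Inputs (Power calculations section).** n = 80; power 0.80; two-sided alpha 0.05. Differences and SDs: fatigue 9 and 20; vertical row 0.09 and 0.20; peakVO2 3 and 7. Planned enrolment: 140 in each exercise group and 120 on the waiting list.

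**2. Reproducing the plan's figures.** Two-sample comparison of means, normal approximation: n per group = 2 × ((1.960 + 0.842) / d)², where d = difference / SD. Power = Φ(d × √(n/2) − 1.960).

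| Measure | d | n per group for 0.80 | Power at 80 per group |
|---|---|---|---|
| QLQ-C30 fatigue | 9/20 = 0.45 | 78 | 0.812 |
| Vertical row | 0.09/0.20 = 0.45 | 78 | 0.812 |
| PeakVO2, ml/min/kg | 3/7 = 0.429 | 86 | 0.774 |

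The fatigue and strength figures reproduce if 80 is per group. Read as a total (40 per group), 80 would give power of only 0.52, 0.52 and 0.48. For peakVO2 the power is about 0.77, but the difference detectable at 80 per group is 2.802 × 7 × √(2/80) = 3.10, which rounds to the stated 3. The arithmetic is therefore not the issue here.

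**3. Matching powered measures to primary measures.**

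| Domain | Primary measure | Powered measure | Match? |
|---|---|---|---|
| Fatigue | MFI, FQL | QLQ-C30 fatigue | No: a secondary instrument |
| Strength | Handgrip, 30-second chair stand | Vertical-row 1-RM/kg | No: not a listed outcome |
| Cardiorespiratory | PeakVO2 in l/min | PeakVO2 in ml/min/kg | Same quantity, different scale |

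**4. What can be said for the primary measures.** No difference or SD is given for MFI, FQL, handgrip, chair stand or peakVO2 in l/min, so their power cannot be computed. In SD units, the difference detectable with 0.80 power is:

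- 80 versus 80: 2.802 × √(2/80) = 0.443 SD
- 140 versus 120: 2.802 × √(1/140 + 1/120) = 0.349 SD
- 140 versus 140: 2.802 × √(2/140) = 0.335 SD

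The last two make no allowance for dropout or clustering.

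**5. Range under assumed effects.** The effects below are assumptions; the document gives none for these measures. Power at 80 per group:

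| Assumed effect (SD) | 0.30 | 0.35 | 0.40 | 0.45 | 0.50 |
|---|---|---|---|---|---|
| Power | 0.47 | 0.60 | 0.72 | 0.81 | 0.89 |

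At full enrolment, an effect of 0.30 SD gives Φ(0.30/√(1/140 + 1/120) − 1.960) = Φ(0.45) = 0.67 for 140 versus 120, and Φ(0.30 × √70 − 1.960) = Φ(0.55) = 0.71 for 140 versus 140, again before dropout and clustering.

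**6. PeakVO2 scale.** For an assumed body weight of 60 to 90 kg, 3 ml/min/kg corresponds to 3 × 60/1000 = 0.18 up to 3 × 90/1000 = 0.27 l/min. The SD of 7 cannot be converted in this way, because the SD in l/min also depends on how weight varies between patients and how it relates to uptake.

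**The case against.** The strongest defence is that 80 per group detects about 0.44 SD on any continuous measure, so a mismatch of instrument does not show that the number is wrong. The plan says openly that its inputs come from one earlier study of a similar programme, and borrowing an effect from a related measure is common. Enrolment is planned well above 80 per group, and the models adjust for baseline values, which generally raises power. All of this stands. It means that the justification is by proxy, not that the sample is too small.

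The defence does not answer the main point. The plan attaches 0.80 power to specific differences on specific measures, and in two domains these are not the measures it calls primary.

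Four stronger readings are tempting and should not be drawn:

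- *That no primary outcome has a power calculation.* PeakVO2 is a listed primary outcome with its own difference and SD. Only the scale conflicts.
- *That the article itself doubts a training effect on handgrip.* The Muscle strength section cites a source to say the opposite: general upper-limb training can raise grip strength. It gives no effect size, so it neither supplies nor rules out the effect assumed for vertical row.
- *That waiting-list patients have no 1-RM value at 12 weeks.* The article does not say so. They start training after 12 weeks, and a test on entry is possible. That vertical row is missing from Table 1 is sufficient.
- *That the trial is underpowered.* A power of 0.47 needs both an assumed 0.30 SD effect and only 80 per group. An effect above 0.45 SD is equally open on these documents.

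**Conclusion.** The point holds for fatigue and muscle strength: the stated 0.80 power belongs to measures that the article does not treat as primary. For cardiorespiratory fitness it reduces to a conflict of units between the outcome definition and the power calculation.

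The consequence for power is unknown rather than adverse. The range in the working depends wholly on effects assumed for illustration, on a simple two-group comparison, and on reading 80 as the number per group, which the plan's own figures require. The documents establish a power claim that does not describe the primary tests in two of three domains. They do not establish that the sample size is inadequate.

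**What to change.** Restate the Power calculations section for the primary outcomes:

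1. For fatigue, name the MFI or FQL score on which the trial is powered. Give the detectable difference (about 0.44 to 0.45 SD at 80 per group) in that score's units, with its SD and the source.
2. For strength, do the same for handgrip in kilograms and for the number of chair stands, and remove vertical row as the basis.
3. For peakVO2, choose one scale and use it in both the Cardiorespiratory fitness section and the power section, with a difference and SD on that scale.

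The cost is a rewritten paragraph and a search for suitable SDs. No patients or measurements are added. The drawback is that the detectable differences, once stated in the units of the primary measures, may look less favourable than the present ones.

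### The sample-size chain does not add up: 80 per group plus 40% is 112, not 120, and 80 per group falls slightly short of 80% power for the printed peakVO2 difference, a smaller gap that rounding may explain

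*Protocol article*

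**What the plan says.** Everything is in the Power calculations section of the protocol article.

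- **Fatigue.** The base figure is introduced so: "With a sample size of 80 we are able to detect a difference in fatigue of 9 points (EORTC QLQ-C30"). The inputs behind it are an SD of 20, 80% power and a two-sided 5% level.
- **Strength and fitness.** The text adds "Additional power calculations (a power of 0.80 and alpha of 0.05) for muscle strength (vertical row) and cardiorespiratory fitness" (peakVO2) and says these "showed that this sample size enables us to detect a difference in vertical row" of a given size. The values are "a difference in vertical row of 0.09 1-RM/kg (SD 0.20") for strength and a difference "of 3 ml/min/kg (SD 7") for peakVO2.
- **Inflation.** To allow for dropout and the multilevel design, "we aim to enrol 40% more patients, therefore in total 120 subjects per group".
- **Final sizes.** Because a smaller contrast is expected between the two exercise intensities, "we have decided to enlarge these two groups to 140 subjects per group". The waiting list group stays at 120.

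**The concern.** The section presents 120 as the direct result of adding 40% to the base, and the only base it gives is 80. Those three numbers cannot all be right. It also says the same 80 gives power 0.80 for all three measures, yet the peakVO2 effect is smaller in SD units than the other two, so one sample size cannot sit at 80% for all of them if the inputs are exact.

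What is at stake is whether the justification can be read and checked. PeakVO2 is the only one of the three powered measures that Table 1 lists as a primary outcome measure; the fatigue calculation uses the EORTC QLQ-C30 and the strength calculation uses the vertical row. A reader also cannot tell what allowance 120 contains. It leaves room for an effective loss of 1 − 80/120 = 33% if 80 are needed, but only 1 − 86/120 = 28% if 86 are needed.

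**Working it through.** **Inputs**, all from Power calculations: base 80; power 0.80; alpha 0.05, two-sided for fatigue and not restated for the other two; fatigue 9 with SD 20; vertical row 0.09 with SD 0.20; peakVO2 3 with SD 7; inflation 40%; result 120 per group; final sizes 140, 140 and 120.

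**Step 1. Reproduce the plan's own figures.** For two equal groups, n per group = 2(1.960 + 0.842)² / d² = 15.70 / d², where d is the difference divided by the SD.

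| Measure | d | n per group, normal | n per group, t-test | Power at 80 per group, t-test |
|---|---|---|---|---|
| Fatigue | 9/20 = 0.450 | 77.5 | 78.5 | 80.8% |
| Vertical row | 0.09/0.20 = 0.450 | 77.5 | 78.5 | 80.8% |
| PeakVO2 | 3/7 = 0.429 | 85.5 | 86.4 | 76.9% |

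Fatigue and vertical row reproduce at 80 per group. This also settles how to read 80: as a total (40 per arm) the fatigue power would be only 51% to 52%. PeakVO2 does not reproduce. The normal approximation gives 77.4% at 80 per group, and 80% needs 86 (normal) or 87 (t-test). A one-sided alpha does not recover the stated figure either; it gives 85.7% (normal).

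**Step 2. Allow for rounding of the peakVO2 inputs.** At 80 per group and 80% power (t-test) the detectable effect is 0.4457 SD.
- With SD 7: 0.4457 × 7 = 3.12 ml/min/kg, which rounds to 3.
- With a difference of 3: the SD would have to be 3 / 0.4457 = 6.73, which rounds to 7.

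So unrounded inputs close to those printed would give 80%.

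**Step 3. The inflation.**
- 80 × 1.40 = 112.
- 120 / 80 = 1.50, a 50% increase.
- Splitting the 40% into two successive increases gives about 114 to 115, for example 80 × 1.20 × 1.20 = 115.2.
- 86 × 1.40 = 120.4.

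No reading of a 40% increase takes 80 to 120. The same increase on the peakVO2 requirement does reach it.

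**Step 4. What the final sizes deliver.** Take exercise versus control on peakVO2 (3 with SD 7, taken as exact) at 140 versus 120, and divide out the inflation to obtain the effective numbers.
- Factor 1.4: 140/1.4 = 100 and 120/1.4 = 86. Power is about 83%.
- Factor 1.5: 140/1.5 = 93 and 120/1.5 = 80. Power is about 80%.

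**The case against.** The strongest reply is that the peakVO2 gap lies within printed precision. The section gives whole numbers and speaks of what the sample can detect, and 3.12 rounds to 3. That stands: the 77% holds only if 3 and 7 are exact, so this part is a discrepancy to clarify and not a proven error. The planned adjustment for baseline values (Statistical analysis) could also lower the requirement, though the article states no correlation from which to compute it. Neither argument touches 112 against 120.

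Four stronger readings are tempting, and the document does not support them.

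- **The trial is underpowered for peakVO2.** The 77% belongs to 80 per group, not to the final design. The slip runs in the safe direction, since 120 exceeds 112 and the exercise groups rise to 140.
- **A 40% loss is planned, so 80/0.6 = 134 are needed, or only 72 of 120 would remain.** The text speaks of enrolling 40% more, which is a multiplication, and ties it to dropout and the multilevel design together. It nowhere assumes a 40% loss.
- **PeakVO2 set the base at 86.** The fit of 86 × 1.4 to 120 is suggestive, but 86 does not appear in the article, 80 is attached to fatigue, and the peakVO2 calculation is described as additional. Only the authors can confirm it.
- **The missing per-group label on 80 and the undivided 40% are defects.** The per-group reading follows from the arithmetic and from the sentence on 120, and an article may leave the split between dropout and design effect to the full protocol.

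**Conclusion.** The point holds as an error of documentation. The base of 80, the 40% and the 120 per group are mutually inconsistent: the stated step gives 112, which is 8 fewer than printed. This is certain from the text and needs no assumption beyond reading 80 as per group.

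The peakVO2 mismatch is smaller and less certain: about 3 percentage points of power, or 0.12 ml/min/kg in the detectable difference. It rests on a two-sample comparison at two-sided 0.05 without covariate adjustment and on taking the printed 3 and 7 as exact.

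Neither part shows that the enrolment target is too small. For exercise versus control, peakVO2 power is about 80% to 83% at the final sizes, provided that losses and clustering together do not exceed the allowance.

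**What to change.** Restate the figures in Power calculations so that they agree, and leave enrolment at 140, 140 and 120. Either of these would do:

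1. Keep 80 per group as the base, describe 120 as a 50% increase, and give the detectable peakVO2 difference as 3.1 ml/min/kg with SD 7 (or state 77% power for 3.0). Note that this describes 80 versus 80, before the exercise groups are enlarged.
2. If the authors confirm that peakVO2 determined the base, state 86 per group for 3 ml/min/kg (SD 7) at 80% power, and keep the 40% increase to 120.

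If the peakVO2 inputs were rounded for print, giving them to one more decimal would settle that part.

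The cost is a sentence or two of rewording. No enrolment target, outcome or analysis changes; under the first option one stated figure becomes slightly less favourable.

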### Recruitment and randomization

The patients are recruited from three hospitals in the southern part of the Netherlands: Máxima Medical Center (Veldhoven/Eindhoven), Catharina Hospital (Eindhoven), and Elkerliek Hospital (Helmond). Expectations are that more hospitals in the southern part of the Netherlands will be invited to collaborate.

In consultation with the treating medical oncologist, the oncology nurse determines if patients in their clinical setting are eligible for the study. All potentially eligible patients receive written information to take home. Next, patients are contacted by telephone and invited to query any question about the study. Patients who are willing to participate are asked to provide written informed consent.

After completing all baseline measurements, patients are stratified by tumour type and hospital and randomly assigned to one of the following groups: 1) high intensity exercise programme or 2) low-to-moderate intensity exercise programme. Next, patients from both groups are randomly assigned to immediate training or waiting list (i.e. waiting list control group). After 12 weeks, patients of the waiting list control group start with the exercise programme they have been allocated to. The research assistant uses statistical software for randomization of the sample and informs patients about the results. Allocation sequence is concealed from the medical team. Study outcomes are assessed by a blinded professional and patients are instructed not to reveal their treatment allocation.

Patients who choose not to participate in the REACT study are asked to complete a one time survey. This questionnaire includes relevant characteristics, the reason for not participating and questions on the current attitudes towards and beliefs about exercise.

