#### Waiting list control group

The control arm of this trial consists of a waiting list in order to control for spontaneous recovery over time. Patients from the waiting list control group start either with the high intensity exercise programme or the low-to-moderate intensity exercise programme after 12 weeks.

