## Discussion

This project aims to contribute to evidence-based practice in cancer rehabilitation programmes. We evaluate the effectiveness of exercise in cancer patients with respect to improving physical fitness and reducing fatigue. Preliminary results in the literature are promising. Yet, the suggested positive physical and psychosocial outcomes of exercise programmes among cancer patients need to be confirmed in large, well-designed trials.

The REACT study evaluates the effectiveness and cost-effectiveness of a high intensity exercise programme compared to a low-to-moderate exercise programme, and a waiting list control group. In this way, we will obtain more insight in outcomes of different training intensities. Furthermore, if exercise appears effective, it becomes vital to evaluate cost-effectiveness and cost savings for health care utilization since exercise-based rehabilitation programmes do not yet form part of standard cancer care for cancer patients and survivors.

The following suggestions made by the systematic reviews have been incorporated to strengthen our methodology; applying a larger sample and long-term follow-up measurements, incorporating randomization of patients to appropriate comparison groups, including concealed allocation and blinded outcome assessment, and using intention-to-treat and per protocol analyses. Most studies so far have focused on breast cancer patients [16-18]. The inclusion criteria of the present study include as many as four cancer diagnoses (primary breast, colon or ovarian cancer, or lymphomas) allowing to explore whether patients with different cancer types respond differently to exercise. Furthermore, detailed evaluation of current attitudes towards and beliefs about exercise of both responders and non-responders are obtained. This provides insight concerning the generalizability of the results from this RCT.

Limitations of the study should be noted as well. Instead of a 'true' non-exercising control group, the present study includes a waiting list control group. Due to the growing availability of cancer rehabilitation groups in daily clinical practices in the study region, patients' expectations may not be met, and higher drop-out rates could occur with a non-exercising control group. However, the use of a waiting list control group does not allow long-term follow-up measurements, because after 12 weeks these patients start the exercise programme they have been allocated to.

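### Waiting-list patients are randomised to an exercise intensity and trained by about week 24, but the three-arm plan gives them no role in the week-64 comparison of intensities

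*Protocol article*

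**What the plan says.** All references are to the protocol article.

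- **Randomisation.** Recruitment and randomization (and the Abstract) describe two steps. Patients are first allocated to an intensity, after stratification by tumour type and hospital. Then "patients from both groups are randomly assigned to immediate training or waiting list".
- **Waiting list.** These patients "start either with the high intensity exercise programme or the low-to-moderate intensity exercise programme after 12 weeks". Recruitment and randomization makes clear that this is the programme they were already allocated to.
- **Arms.** The Intervention section nevertheless describes three arms: high intensity, low-to-moderate intensity and waiting-list control.
- **Hypothesis.** The Background expects high intensity to do better than low-to-moderate intensity in both the short term and at one-year follow-up.
- **Sample size.** Each group is first set at 120. Because a smaller difference is expected between the intensities, "we have decided to enlarge these two groups to 140 subjects per group"; the waiting list stays at 120. No effect size or time point is attached to the 140.
- **Measurement times.** The Abstract and Study Outcomes set t1 at 12 weeks and t2 at 64 weeks after randomisation, with no exemption for the waiting list. The Discussion, under limitations, says that "the use of a waiting list control group does not allow long-term follow-up measurements", because these patients start exercising after 12 weeks.
- **Model.** Statistical analysis fits t1 and t2 outcomes in one multilevel model, with coefficients described as differences between the interventions and the control group.

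**The concern.** The allocation is a two-by-two structure, intensity by start timing, which the plan collapses to three arms. That is sensible at t1, when the waiting list is the only untrained group. It is not sensible at t2. By then the waiting list is no longer a control for exercise: it consists of two groups that have each been through a randomised intensity. A single control coefficient carried across both time points has no clear meaning at week 64.

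The Discussion's reason for giving up long-term data on these patients applies to exercise versus no exercise. It does not apply to high versus low-to-moderate intensity, where having received the programme is exactly what makes them informative. That long-term contrast is a stated hypothesis, and it is the one for which the plan itself expects the smaller difference. Followed as written, the plan either leaves up to 120 of 400 randomised patients out of it or uses a trained group as a control.

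**Working it through.** **Inputs from the Power calculations section.** Fatigue difference 9 points, SD 20, "a power of 0.80 and two sided alpha of 0.05"; base size 80, read as per group; an allowance described as 40%, giving 120; then 140 + 140 + 120 = 400.

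**Reproducing the plan's base figure.** n per group = 2 × ((1.960 + 0.842) × 20/9)² = 77.5, so 78 by the normal approximation and 79 by the t-test. The stated 80 reproduces. The 140 has no stated inputs, so it cannot be derived or faulted.

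**Timing.** Waiting-list patients start at week 12 and train for 12 weeks, finishing at about week 24. At week 64 they are 64 − 24 = 40 weeks past the end of the programme; immediate starters are 64 − 12 = 52 weeks past it.

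**Numbers per intensity at t2.** The split of the 120 by intensity is not stated. Assuming 60:60, each intensity has 140 + 60 = 200 enrolled.

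**Standard error.** The ratio for equal arms is √(140/200) = 0.837, a fall of about 16%. With stratification by start timing and a split of a:b, the ratio is √(70 / (70 + ab/(a + b))), where 70 = 140 × 140/280:

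| Split of the 120 | SE ratio |
|---|---|
| 60:60 | 0.837 |
| 50:70 | 0.840 |
| 40:80 | 0.851 |

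The gain hardly depends on the split.

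**Detectable fatigue difference.** SD 20, two-sided 0.05, power 0.80, two-sample t-test. The normal approximation, 2.802 × 20 × √(2/n), is in brackets. The article describes its allowance as 40%, but 120/80 = 1.5, so both deflators are shown.

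| Basis | 140 per intensity | 200 per intensity |
|---|---|---|
| Enrolled ÷ 1.4 | n = 100: 7.96 (7.92) | n = 143: 6.65 (6.63) |
| Enrolled ÷ 1.5 | n = 93: 8.24 (8.20) | n = 133: 6.89 (6.86) |
| No deflation | 6.72 (6.70) | 5.62 (5.60) |

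**Illustrative power.** For a true difference of 4.5 points, half of the 9 and an assumption not found in the article, power with the 1.4 allowance rises from 35% to 47%.

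**Sensitivity of an intensity-by-timing check.** With the 1.4 allowance, 100 immediate and 60/1.4 = 43 delayed starters per intensity give an interaction SE of 20 × √(2/100 + 2/42.9) = 5.16. The detectable interaction is 2.802 × 5.16 = 14.5 points, about twice the detectable main effect.

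**At t1.** The waiting list is untrained and adds nothing to the intensity contrast, which stays at 140 per group.

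**The case against.** Three stronger readings are tempting, and the article does not support them.

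- **A reader might infer that the long-term comparison was sized on 140 per arm and that this is an error.** The Power calculations section names no time point for the 140. The intensity hypothesis also covers the short term, where 140 is the correct count.
- **A reader might infer that the extra patients come at no cost.** That requires t2 visits in the waiting list. The Abstract and Study Outcomes imply them; the Discussion, read literally, denies them, although it may mean only that no untrained comparator remains. If these visits are not planned, adding them means further central physical testing, including the maximal exercise test.
- **A reader might infer that the plan deliberately discards 30% of its patients (120/400).** No section says they are excluded from a t2 intensity comparison. The article simply assigns them no part in one, and a fuller analysis plan might do so.

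There is also a substantive objection: pooling shifts the question. Delayed starters are about 40 rather than 52 weeks past training and begin it about 12 weeks further into recovery from chemotherapy. Stratification removes the main effect of timing but does not make the intensity effect equal in the two start groups, and the interaction check is weak. This stands as a real limitation, and taking immediate starters as the primary t2 set would be defensible. It does not introduce bias: intensity is randomised before timing, so a comparison within start-timing strata is protected, and the pooled estimate is an average over two start timings.

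The objection that contrast membership is detail for the analysis plan stands only in part. The three-arm structure, the joint t1/t2 model and the conflicting statements on follow-up are all in the article itself.

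**Conclusion.** The point holds as a missed efficiency and an undefined role for the waiting list at t2, not as a sample-size error. If t2 is collected in waiting-list patients, analysing by randomised intensity raises the long-term contrast from 140 to about 200 enrolled per intensity and cuts its SE by about 16%. The detectable fatigue difference falls from about 8.0 to 6.7 points with the 1.4 allowance, or from 8.2 to 6.9 with the 1.5 ratio. The gain is useful but modest: under the illustrative 4.5-point difference, power stays below 50%. The size rests on a roughly even split of the 120 (not critical), on similar loss to follow-up in both start groups, and on t2 data being available, which the article leaves unsettled. Nothing changes at t1. The change is worth making, because the plan as written gives no interpretable t2 contrast for these patients.

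**What to change.** 1. Reconcile the Abstract and Study Outcomes with the Discussion, and state whether waiting-list patients are assessed at week 64.
2. Restrict the exercise-versus-waiting-list contrast to t1, so that no single control coefficient spans t1 and t2.
3. Provided t2 is collected in waiting-list patients, compare high with low-to-moderate intensity at t2 in all patients by randomised intensity, stratified by start timing.
4. Report an intensity-by-timing check, described as low-powered, and a sensitivity analysis in immediate starters only.
5. Keep 140 per group for the t1 comparison, and say that the t2 estimate averages over immediate and delayed starts.

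Cost: wording of the analysis only, if t2 visits in the waiting list are already planned. If they are not, the cost is the week-64 assessments for up to 120 patients, to be weighed against the gain above.
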